### Outcome measurement

The main outcome measures in the trial are the differences between the number of days with migraine and intensity of headache in the headache diaries during 4 weeks before randomization and 4, 8, and 16 weeks after randomization. The intensity of headache includes the Headache intensity grade (0–3) and visual analogue scale (VAS) score (0–10). The secondary Outcome Measures are the differences in frequency of migraine attacks (episodes of migraine headaches separated by pain free intervals of at least 48 hours), average duration of a migraine attack, rate of rescue medication used, number of patients with adverse side effects, Migraine-Specific Quality-of-Life Questionnaire (MSQ) before randomization and 4, 8, and 16 weeks after randomization, and the differences in Transcranial Doppler Sonography (TCD) before randomization and 4 weeks after randomization.

All patients fill in headache diaries during 4 weeks before randomization (baseline phase) and 4, 8, and 16 weeks after randomization. In the diaries they document the time of attack and stopping of headache, the intensity, the frequency, the location and the cause of headache, associated symptoms in each migraine attack. The patients document whether or not they take the medicine during treatment periods, and if patients take medicine they have to document the name, dosage of the medicine, the time of taking medicine, the time of relieving pain and the side effect of the medicine. In addition, all patients will accept routine test of blood, urine and stool, and electrocardiogram (ECG), liver function (ALT, AST), kidney function (BUN, Scr) before randomization, in order to exclude these patients who have serious illness in heart, liver and kidney or other severe disease.

Any adverse events, and how they are addressed, are recorded during the four treatment weeks and twelve follow-up weeks. These adverse events include bleeding, hematoma, fainting, serious pain, and local infection. If patients suffer any serious adverse events, all details will be documented.

All acupuncturists are required to attend special training classes in order to understand the details of this trial. The special training classes have theoretical lessons and practical lessons. All people have to understand the purpose and content of the trial, treatment strategies and quality control. For instance, they are trained to know how to use the central randomization method, how to fill in the CRF (case report form) and electro-CRF, how to locate the points and manipulate the needles, etc. The acupuncturists must take part in all of the training classes as well and have to pass the special training test before they are qualified to perform this trial. Additionally, in order to keep quality control, a special quality examination form is made for checking the whole processes of the trial and documenting the details of the processes. This work is performed by the special trained checkers once a month in every hospital in the centers.

Drop-outs or withdrawals and their reasons, and patient's compliance have to be documented during the four treatment weeks and twelve follow-up weeks. All patients are recorded until the end of the trial.

### Statistical analysis

Analysis of all data in this trial will be performed by the National Clinical Trial Center of Chinese Medicine (Chengdu GCP Center) in China, which is performed in a blinded manner because analysis of data is done by a special analysis-researcher. The data will be analyzed with SPSS13.0 and SAS9.0 statistical software packages.

The intention-to-treat (ITT) population is defined as the patients who are randomized. The data analysis of baseline characteristics is based on the intention-to-treat (ITT) population. And the data analysis of the primary and secondary outcomes and other outcomes is mainly based on the intention-to-treat (ITT) population. In addition the per-protocol (PP) population is analyzed. The result of the ITT analysis will be compared with that of the PP analysis to check whether the results are consistent.

The first step of analysis is to make comparisons among baseline characteristics in different groups. The second step is to check whether acupoints treatment groups were more efficacious in treating migraine than non-acupoints control group. If acupoints treatment is more effective than non-acupoints treatment in treating migraine, the third step is to make comparisons among three acupoints treatment groups in effectiveness of treating migraine.

For normal distribution data (normality, homogeneity of variances) the repeated measures analysis will be used in the different time-points assessment. The Kruskal-Wallis test will be employed in the analysis of skewed distribution data. Moreover, analysis of variance (ANOVA) and used for numerical variables, Chi-square test is used for categorical variables. Two-sided test is applied for all available data, and a P value < 0.05 is considered statistically significant.

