**Methods and design:**

A multi-center randomized controlled trial is currently undergoing, with three acupoints treatment groups and one non-acupoints control group. The acupuncture treatment consists of 20 sessions per patient with a observation period of 20 weeks. In total, 480 patients with Migraine are registered in this study within 8 hospitals in China from March 2008 to June 2009. These patients are randomly assigned to receive one of the following four acupoints treatment groups, i.e. 1) specific acupoints of Shaoyang meridians (120 patients), 2) non-specific acupoints of Shaoyang meridians (120 patients), 3) acupoints of other meridians (120 patients); or 4) non-acupoints control group (120 patients). The main outcome measurement in this trial is the effect comparison achieved among these four groups in terms of number of days with migraine and intensity of migraine during and after the baseline phase, i.e. the first 4 weeks before randomization and 4, 8 and 16 weeks after randomization. The intensity of headache including Headache intensity grade (0–3) and visual analogue scale (VAS) score will also be used in this study. In addition, the differences of Migraine-Specific Quality-of-Life Questionnaire (MSQ) and Transcranial Doppler Sonography (TCD) before and after randomization are also used as the secondary outcome measurement.

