### Patients

A power analysis is calculated before conducting this trial, which *α *= 0.05 and power = 90%. According to the previous literature [7], for the main outcome the number of days with migraine, an improvement of 2.4 days by sham acupuncture is reported. In this study, we anticipated an improvement of 4.0 days by acupuncture, so a difference of 1.6 days is considered minimally of clinical significance. Therefore, the sample size in this trial can be estimated initially according to the following formula [10]. Each group needs at least 120 patients (assuming a 15% dropout rate), 480 patients in four groups totally will be enrolled in the study.

$$n=\frac{\psi^{2}(\sum_{j=1}^{k}s_{j}^{2}/k)}{\sum_{j=1}^{k}{\left({\bar{x}}_{j}-\bar{\bar{x}}\right)}^{2}/(k-1)}$$

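### The main outcomes are changes from a baseline diary, but none of the named analyses has a stated baseline covariate; adjusting for baseline would gain precision at no cost in data

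*Protocol article*

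**What the plan says.** **Outcome.** The section Outcome measurement states: "The main outcome measures in the trial are the differences between the number of days with migraine and intensity of headache", taken from the diaries in the 4 weeks before randomization and at 4, 8 and 16 weeks after it. These are changes from baseline. The section Patients sizes the trial on the same scale: "an improvement of 2.4 days by sham acupuncture is reported" and "we anticipated an improvement of 4.0 days by acupuncture, so a difference of 1.6 days is considered minimally of clinical significance".

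**Availability of baseline.** A completed baseline diary is an inclusion criterion, so every eligible patient has the value.

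**Analysis.** The section Statistical analysis assigns repeated measures analysis to the time-point assessments when data are normal, and Kruskal-Wallis when they are skewed. It then adds a general line: "analysis of variance (ANOVA) and used for numerical variables, Chi-square test is used for categorical variables". No method is given a baseline covariate or a hospital term. Baseline is otherwise mentioned only as a preliminary: "The first step of analysis is to make comparisons among baseline characteristics in different groups". No later step uses the result of that comparison.

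**Centres.** The Abstract reports that "480 patients with Migraine are registered in this study within 8 hospitals in China". The Discussions section describes central, complete randomization; no stratification by hospital is stated.

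**The concern.** In a randomized trial with a quantitative baseline, a change score fixes the slope of follow-up on baseline at 1. When the true slope is lower, as it is with equal variances and a correlation below 1, subtraction over-corrects and adds noise. A covariate lets the data estimate the slope.

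Two things follow. Confidence intervals are wider than they need be. And part of any chance baseline difference between groups stays in the treatment contrast, because the group that starts higher tends to fall further whatever the treatment. Patients are selected on having at least two attacks a month, so some regression to the mean is to be expected.

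Precision matters most in the third analysis step, which compares the three acupoint groups with one another. Those differences may well be smaller than the 1.6 days assumed against control.

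**Working it through.** **Inputs from the documents.** Two-sided alpha 0.05, power 90%, difference 1.6 days, 120 per group, 15% dropout, eight hospitals. **Not in the documents, so assumed:** rho between 0.3 and 0.8, and a hospital share of variance between 1% and 10%. The SD is not given either and is back-solved below.

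**1. The plan's own figure.** 120 × 0.85 = 102 evaluable, and 102/0.85 = 120, so the dropout step is consistent. The 120 itself can be neither reproduced nor refuted, because the formula needs an SD and a pattern of four means and neither is stated. Back-solving at 102 evaluable and 90% power:
- Pairwise comparison: SD = √(102/2) × 1.6/(1.960 + 1.282) = 3.52 days.
- The article's four-group formula (psi = 2.173) with means 4.0/4.0/4.0/2.4: SD = √(102 × 0.64/2.173²) = 3.72 days. For 4.0/3.2/3.2/2.4 it is 3.04, and for two groups against two it is 4.29.

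The pairwise value is used below, so that the unadjusted change-score comparison has exactly 90% power.

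**2. Variance at one visit** (equal variances s²):
- change score: 2(1−rho)s²
- baseline-adjusted: (1−rho²)s²
- ratio: (1+rho)/2

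The direction does not depend on equal variances. With baseline SD s0 and follow-up SD s1, the change-score variance minus the adjusted variance is (s0 − rho·s1)², which is never negative. Only the size depends on the assumption.

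**3. Power at 102 per group.** Power = Φ(3.2415/√ratio − 1.960).

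| rho (assumed) | Variance ratio | Reduction | Power | Evaluable (enrolled) per group for 90% |
|---|---|---|---|---|
| 0.3 | 0.65 | 35% | 98.0% | 67 (79) |
| 0.5 | 0.75 | 25% | 96.3% | 77 (91) |
| 0.7 | 0.85 | 15% | 94.0% | 87 (103) |
| 0.8 | 0.90 | 10% | 92.7% | 92 (109) |

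The last column is a yardstick, not a proposal to enrol fewer patients.

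**4. Does repeated measures analysis remove the loss?** Take the mean of three follow-up visits with a common correlation rho, in units of s²:
- change: (1+2rho)/3 + 1 − 2rho = 4(1−rho)/3
- adjusted: (1+2rho)/3 − rho² = (1−rho)(1+3rho)/3
- ratio: (1+3rho)/4 = 0.475, 0.625 and 0.775 at rho 0.3, 0.5 and 0.7

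If baseline is entered as a time point in a classical repeated measures analysis, the group contrast of follow-up against baseline is this same change score. If only raw follow-up values are modelled, the variance is (1+2rho)/3; at rho 0.5 that is 0.667 against 0.417 adjusted, again a ratio of 0.625. On each reading, adjustment is more precise for any rho between 0 and 1.

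**5. Chance imbalance.** If one group starts d days higher by chance, the expected shift in its change-score contrast is rho·d − d = −(1−rho)d. Per day of imbalance that is 0.7, 0.5 and 0.3 days at rho 0.3, 0.5 and 0.7. A baseline-adjusted contrast has no such expected shift.

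**6. Hospital.** If hospitals carry a share h of the variance, a hospital term multiplies the residual variance by (1−h). From the same 90% start, power becomes 90.3% at h = 1%, 91.4% at 5% and 92.7% at 10%: a gain of 0.3 to 2.7 points.

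**The case against.** **The article condenses the plan.** Covariates are model detail that a protocol article commonly leaves to the SAP, which is not shown, and nothing here excludes them. Defining the outcome as a difference does not bar adjustment either: ANCOVA on change with baseline as covariate gives the same group contrast as ANCOVA on follow-up. This stands as a reason to treat the point as an improvement rather than an error. It does not dispose of it, because the article positively names its methods. Kruskal-Wallis as named takes no covariate, and ANOVA takes no continuous one. Day counts in a 4-week window are bounded and may be skewed, so the article's own rule could send the main outcome to Kruskal-Wallis.

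**Stronger readings that the documents do not support:**
- *The main outcomes are compared by ANOVA.* The ANOVA sentence is a general line for numerical variables. The time-point sentence on repeated measures fits outcomes measured at baseline and three later visits better.
- *Baseline is ignored.* A change score uses baseline, though inefficiently, and baseline may also enter as a time point. The article does not say.
- *The treatment comparison is biased or invalid.* An unadjusted change-score comparison in a randomized trial is unbiased over repeated randomization. Chance imbalance adds variance.
- *Leaving out hospital is a validity error.* No stratification by hospital is stated, so a hospital term is a matter of efficiency, and the gain is small.
- *The first-step baseline comparison does harm.* The article names no test for that step, and no later step depends on it. Its general line, "Two-sided test is applied for all available data, and a P value < 0.05 is considered statistically significant", makes significance testing plausible, but this does not affect the treatment contrast.
- *The loss of power is large.* Assuming an effect well below the planned 1.6 days can make the gain look much larger. That would not describe this design.

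**Conclusion.** The point holds as a matter of precision. The main outcomes are framed as change from baseline, and the article names only methods without a stated baseline covariate, although every patient must supply the baseline value. Adjustment lowers the variance at one visit by 10% to 35% for assumed rho of 0.8 to 0.3. It raises power from 90% to about 93% to 98% at 102 evaluable patients per group, and it protects the contrasts against chance baseline imbalance.

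The size rests on an assumed rho, equal variances, a pairwise comparison of means, and an unadjusted analysis that has exactly the stated power. The documents give neither rho nor an SD, so the range is illustrative. It does not cover a Kruskal-Wallis analysis. The direction of the result is secure; the amount is not.

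**What to change.** In the section Statistical analysis, prespecify one primary model for the main outcomes: an ANCOVA, or a mixed model across visits, of the follow-up values with that outcome's own baseline diary value as covariate. Report adjusted group differences with 95% CI. Hospital may be added as a factor for a small further gain.

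The cost is plan wording only. The baseline diary and the hospital are already recorded for every patient, and no visit, measurement or sample size changes.

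### Three unranked main outcomes at three time points, all tested at an unadjusted P < 0.05, do not hold the 5% error rate at which the trial was sized on migraine days alone

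*Protocol article*

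**What the plan says.** **Sample size (Patients).** The calculation concerns one variable, "for the main outcome the number of days with migraine", with "0.05 and power = 90"%. The target difference is 4.0 − 2.4 = 1.6 days, which leads to 120 patients per group with 15% dropout.

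**Main outcomes (Outcome measurement).** Here the wording is plural: "The main outcome measures in the trial are the differences between the number of days with migraine and intensity of headache". Intensity is itself two scales: "The intensity of headache includes the Headache intensity grade (0–3) and visual analogue scale (VAS) score (0–10"). The measurement times are given as "during 4 weeks before randomization and 4, 8, and 16 weeks after randomization". No variable and no time point is ranked above another. The Abstract likewise lists days, intensity and all three times.

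**Testing (Statistical analysis).** The rule is flat and two-sided, for all data: "a P value < 0.05 is considered statistically significant". The analysis runs in steps. Step 2 asks whether the acupoint groups do better than control. If they do, step 3 compares the three acupoint groups with each other. Normally distributed data get a repeated measures analysis over the time points, and skewed data go to Kruskal-Wallis. The section does not say which outcome, time or contrast (pooled or group by group) decides step 2, nor whether one favourable result suffices.

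**The concern.** Two sections disagree on what the main outcome is. One spends the whole 5% on migraine days; the other gives the same standing to three variables at three times. With a flat 0.05 rule and no defined success criterion, a favourable result on any of them could be reported as efficacy.

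The Background presents the trial as an answer to inconsistent earlier results against sham needling. The Discussions section makes acupoint specificity the purpose of the study. Both the efficacy claim and access to the specificity comparisons pass through step 2, so an undefined step 2 weakens both. The condition on step 3 does not cure this, because the multiplicity lies inside step 2.

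**Working it through.** **1. The plan's own figure.** The 120 per group cannot be reproduced, because the article gives neither the standard deviation nor all four group means. It can be back-solved:

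- Evaluable per group: 120 × (1 − 0.15) = 102.
- Two-means formula, n = 2(1.960 + 1.282)² s² / 1.6². Setting n = 102 gives s ≈ 3.5 days.
- The article's k-group formula, n = ψ² s² / variance of means, with ψ ≈ 2.17 (k = 4, alpha 0.05, power 90%). Means of 4, 4, 4 and 2.4 have variance 0.64, so s ≈ 3.7. With the two middle means placed between 2.4 and 4.0, s ≈ 3.0–3.2.

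The size is thus compatible with one test at an unadjusted 0.05.

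**2. Counting the tests in step 2.**

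- Reading A: repeated measures merges the times, one pooled acupoints-versus-control test per outcome: 3 tests.
- Reading B: each time tested separately (for example Kruskal-Wallis on skewed data), pooled contrast: 3 × 3 = 9 tests.
- Reading C: each time separately, each acupoint group against control: 3 × 3 × 3 = 27 tests.

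**3. Upper reference, independent tests.** 1 − 0.95^k gives 14.3% (k = 3), 37.0% (k = 9) and 75.0% (k = 27). The tests are correlated, so these overstate the rate.

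**4. Correlated tests.** Multivariate-normal simulation under no effect, critical value 1.96. The correlations between outcomes and between times are assumptions, since the article gives none. The 0.5 between contrasts follows from equal groups sharing one control.

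| Reading | Tests | Any two-sided P < 0.05: low correlation (0.3 outcomes, 0.5 times) | Same: high correlation (0.8, 0.8) | Favouring acupuncture only: low | Same: high |
|---|---|---|---|---|---|
| A | 3 | 13.6% | 9.8% | 6.9% | 4.9% |
| B | 9 | 31.7% | 18.5% | 16.3% | 9.3% |
| C | 27 | 62.8% | 40.8% | 34.9% | 20.7% |

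The benchmark is 5% for the two-sided columns and 2.5% for the favourable-only columns. If reading A uses a four-group omnibus test per outcome instead of a pooled contrast, the two-sided rate is almost the same: 13.7% and 10.2% at outcome correlations of 0.3 and 0.8.

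**5. Does fixing the outcome alone suffice?** No. Migraine days at one time, with three groups each against control, gives about 12.5% two-sided. Migraine days at three separate times with a pooled contrast gives about 12.6% (correlation 0.5) to 9.8% (correlation 0.8). Outcome, timing and contrast all have to be stated.

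**6. Why not simply split alpha?** With 102 per group and an assumed SD of 3.5, power for 1.6 days is 90% at 0.05. It falls to 81% at 0.05/3, 69% at 0.05/9 and 56% at 0.05/27. One primary test keeps the planned power.

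**The case against.** The strongest reply is that the plan does not propose 27 tests. For normally distributed data it specifies repeated measures across time. Kruskal-Wallis, ANOVA and the sample size formula are all k-group methods, and separate tests of each group against control are nowhere listed. That stands: a reader might infer an error rate of 41–63%, or even 75%, but the text supports this only as an extreme. The moderate figure is 10–14%. The nine-test reading remains open, because day counts and a 0–3 grade may well be skewed and Kruskal-Wallis gives no single test across time.

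A second reply also stands. Only results favouring acupuncture open step 3, so the two-sided rates should not be read as the chance of a falsely positive trial. That chance is roughly half as large, but its benchmark is 2.5%, so the relative excess is similar.

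A third reply is that a separate analysis plan may define the test and an adjustment. It may, and the absence of such detail here is not the point. The article itself states a flat 0.05 for all data and contradicts itself on the main outcome. If the sample size paragraph is taken as decisive, the outcome section and the Abstract still need correcting.

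Finally, a reader might infer that intensity is undefined in patients who become attack-free. The documents do not support this: the note to Figure 2 in the Design section defines grade 0 as no headache.

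**Conclusion.** The point holds in a moderate form. The article names three co-equal main outcomes at three times, sizes the trial on one of them, tests everything at an unadjusted 0.05 and makes step 3 depend on a result it does not define. On every reading that keeps three main outcomes, the error rate exceeds the one assumed in the sample size. It is about two to three times nominal on the mildest reading, and about four to six times if time points are tested separately. The direction does not depend on the correlations chosen; the size does. The figures assume approximately normal test statistics, no true effect in any group, and that one significant result would be enough to claim success. The article does not exclude that last assumption. The rate returns to 5% only if migraine days is the sole primary outcome, with one test across time (or in one window) and one pooled or omnibus comparison, or an adjusted set of contrasts.

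**What to change.** - Name migraine days as the single primary outcome, in agreement with the sample size paragraph, and align the Abstract and the outcome section with it.
- State one test for it: either one repeated-measures test across the time points, or a comparison in one stated 4-week window. Either controls the error; the former is closer to the existing analysis text.
- State one contrast: pooled acupoint groups against control, or the three groups each against control with a Dunnett or Holm adjustment. The adjusted route costs some power. Bonferroni at 0.05/3, with the assumed SD of 3.5, gives 81% for any one contrast as a cautious guide.
- Make intensity grade, VAS and the remaining time-point comparisons secondary.
- Let step 3 open only on that one primary test.

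**Cost.** No extra patients or data are needed with the pooled contrast. The trial is registered, approved and already under way, so this means a protocol and registry amendment, not just an edit to the text. An isolated positive result on intensity or VAS could no longer carry the trial.
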